## Abstract

**Background:**

Frailty is the deterioration of physiological functions due to aging, linked to negative outcomes. Frailty, being a reversible and dynamic state, calls for individualized and comprehensive management. Goal Attainment Scaling (GAS) is a personalized method for establishing and assessing progress towards individual goals, suitable for older adults with complex requirements. We focus on attaining personalized intervention goals for elderly patients with frailty, correcting frailty manifestations, maintaining enhanced functional capacity, and cultivating sustainable health awareness, with the goal of improving overall quality of life.

**Methods:**

We conducted a randomized clinical trial of an individualized intervention program using GAS as goal setting and evaluation method designed to improve physical functional in frailty elderly. A total of 160 individuals aged ≥ 60 years, who fulfill the Fried scale of frailty will be recruited from Beijing Chaoyang Hospital, Capital Medical University. All participants set personalized goals through GAS. Patients in the intervention group receive individualized interventions, implement tailored measures based on personalized goals, attain personalized intervention goals to improve or reverse the frailty state. The participants will be followed up for 3 months and 12 months.

**Discussion:**

The advantage of the present study is the method of intervention. Personalized interventions will implement based on patient-specific needs through individualized goal-setting formulated according to the GAS. If a positive consequence could be obtained, this study’s findings will offer essential information for managing frailty in older adults, applicable in regular clinical settings.

**Ethics and trial registration:**

The trials have received ethics approval from the Institutional Review Board for Human Studies of Beijing Chaoyang Hospital, Beijing, China. The clinical study is supported by the National Health Commission of the People’s Republic of China (2024YB53). We declare that the funding agency has independently reviewed the protocol as part of the process of awarding funding. The trial is registered as ClinicalTrials.gov Identifier: NCT06919575 (Registration Date: 2025-04-02).

**Supplementary Information:**

The online version contains supplementary material available at 10.1186/s12877-025-06203-1.

## Background

The world’s population is getting older as average life expectancy rises, with 21.3% expected to be 60 or older by the year 2050. Healthcare systems are facing a growing challenge with higher demand because of the aging population, with frailty among older adults is becoming more common worldwide. Literature reported that the prevalence of frailty and pre-frailty in older adults was 17.4% and 52.6%, respectively [1]. Efforts to reduce the burden of frailty could have substantial public health consequences [2, 3].

Increasing attention is being paid to the growing prevalence of frailty in older adults. Frailty involves a notable reduction in the functional reserve of various organ systems, making individuals more susceptible to stressors, resulting in a greater risk of adverse health outcomes, including falls, disability hospitalization and mortality among older adults [4–10]. Thus, enhancing the functional abilities of frail older adults and potentially reversing their frailty is of great clinical significance.

Frailty is described as a dynamic transition, that can be improved or reversed. This phenomenon was confirmed by several trials conducted on different types of individuals, and the cost associated to them avoidable, thus preventing imminent future society demands [11–17]. Studies have indicated that frailty transitions are affected by factors such as older age, previous health issues, physical activity and mobility levels, socio-economic and clinical conditions, and vitamin D levels [18–25]. Addressing these changeable factors could improve the functional status of frail elderly people.

Several studies showed that multi-domain interventions of frailty are effective in improving the frail status of individuals [26–33]. Notably, targeted therapies are highly advised over non-specific treatments in precision medicine. However, evidence remains limited regarding personalized frailty intervention protocols tailored to individual clinical profiles.

Frailty people frequently experience a multitude and diversity of health problems that cause functional limitations. Since the impact of these health problems varies from person to person, the priorities and goals of treatment also differ for each older individual. Standardized assessment tools often fail to adequately measure intervention effects across this heterogeneous population. The diversity of patients, diseases and personal goals makes it important to be able to evaluate the attainment of all relevant goals per patient. Given the heterogeneity in individual requirements, personalized intervention strategies should be formulated based on comprehensive geriatric assessments.

Goal setting is a key component of person-centered, individualized interventions. Goal Attainment Scaling (GAS) is a validated outcome measurement tool that facilitates the establishment and quantitative assessment of personalized treatment goals [34–40]. This method is particularly suitable for older adults with multiple chronic conditions and complex needs, as it enables tailored goal setting and structured evaluation of progress. A key feature of GAS is its ability to individualize treatment goals while enabling standardized progress tracking, yielding a quantifiable and comparable score across individuals. As a personalized outcome measure, GAS supports the assessment of multiple patient-specific objectives, including those in tailored interventions. By systematically integrating functional assessments and individualized needs, GAS enhances precision in tracking progress and refining intervention strategies.

We conduct a randomized clinical trial of an individualized intervention program using Goal Attainment Scaling (GAS) as evaluation method designed to Improve physical functional in frailty elderly. Our primary aim focused on attaining personalized intervention goals for elderly patients with frailty, correcting frailty manifestations, maintaining enhanced functional capacity, and cultivating sustainable health awareness, with the goal of improving overall quality of life.

## Methods

### Study design

This randomized parallel controlled trial included a 3-month and 12-month follow-up period. Figure 1 shows the flow diagram of the progress through the phases of this parallel randomized trial of two groups. Participants were recruited from a large general hospital and two community health centers within a medical alliance in Chaoyang District, Beijing. The study protocol received approval from the Institutional Review Board for Human Studies of Beijing Chaoyang Hospital. Funding was provided by the National Health Commission of the People’s Republic of China (Grant No. 2024YB53). The trial is registered at ClinicalTrials.gov NCT06919575 (Registration Date: 2025-04-02).

**Fig. 1 Fig1:**
[figure not shown]
Schematic representation of the randomized controlled trial

### Recruitment

The recruitment process comprises two stages:

Screening Phase: Potential participants aged ≥ 60 years will be screened for frailty at a large general hospital and two community health service centers within a medical alliance. A brief assessment will evaluate inclusion/exclusion criteria, with outpatient clinics serving as the primary recruitment source.Enrollment Phase: Eligible individuals expressing interest will receive detailed study information. Written informed consent will be obtained prior to participation. Recruitment will continue until the predetermined sample size for statistical analysis is achieved.

### Measures of frailty

Frailty will be identified using Fried scale according to its five criteria [41–43]:

Weight loss: defined as unintentional weight loss ≥ 4.5 kg or ≥ 5% of body weight in the last year.Exhaustion: was measured by self-report using two questions: (‘How many days during the last week have you felt that anything you did was a big effort?’ and ‘How many times during the last week have you felt that you could not keep on doing things?’). The criterion was met when participant answered self-reported fatigue ≥ 3 days in the last week.Weakness: based on grip strength, stratified by gender and body mass index (BMI) quartiles. For men, BMI ≤ 24 kg/m^2^, grip strength ≤ 29 kg; BMI 24.1–26 kg/m^2^, grip strength ≤ 30 kg; BMI 26.1–28 kg/m^2^, grip strength ≤ 30 kg; BMI >28 kg/m^2^, grip strength ≤ 32 kg. For women, BMI ≤ 23 kg/m^2^, grip strength ≤ 17 kg; BMI 23.1–26 kg/m^2^, grip strength ≤ 17.3 kg; BMI 26.1–29 kg/m^2^, grip strength ≤ 18 kg; BMI > 29 kg/m^2^, grip strength ≤ 21 kg. In this study, we will measure the grip strength of the dominant hand twice to obtain the average.Slowness: was defined using the 6 m walking test at their usual pace, ≤ 1.0 m/s is considered abnormal. Best time of two performances was chosen.Low physical activity: defined as energy expenditure of physical activity per week <383 kcal for men or <270 kcal for women.

The presence of ≥ 3 criteria is defined as frailty.

### Inclusion and exclusion criteria

The inclusion criteria were the following: (1) ≥ 60-years old; (2) recognized as frailty by Fried scale.

The exclusion criteria were the following: (1) considered with life expectancy <1 year such as advanced cancer patients; (2) difficult to communicate with such as patients with severe cognitive impairment (Mini Mental State Examination score ≤ 17); (3) severe hearing discord.

### Randomization

Once a patient fulfills the criteria, after informed consent, participants will be randomly assigned to either the Usual care group or the Intervention group based on random number at a 1:1 ratio generated in a blinded manner by the computerized randomization system. The information of random group allocation will be maintained in a sealed envelope opened only by a trial manager who is not involved in the recruitment, assessment, or intervention to assign the treatment. The control group will receive routine diagnosis and treatment, while the intervention group will receive individualized interventions.

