## Intervention

First, a comprehensive assessment will first identify the underlying etiologies of frailty (e.g., physical inactivity, malnutrition, or psychological factors) to guide targeted interventions. Individualized treatment goals will be established using Goal Attainment Scaling (GAS), with subsequent implementation of personalized intervention plans. For participants presenting with ≥ 2 concurrent issues, multidisciplinary specialists will coordinate simultaneous management.

Participants identified with malnutrition or mood disorders will undergo standardized nutritional assessment (e.g., Mini Nutritional Assessment) and psychological evaluation (e.g., Geriatric Depression Scale). Evidence-based nutritional supplementation and/or pharmacotherapy will be initiated according to established clinical guidelines when indicated.

The patients of the intervention group with poor physical function would receive exercise prescription tailored to the subjects’ physical ability from a trained specialist. For Participants requiring exercise-based interventions, a moderate and gradually increasing intensity exercise regimen home-based, three times a week will be administer under telehealth-based monitoring. A standardized protocol exercise intervention comprises a 20-30-minute session with progressive phases, over a 12-week duration: 5-minute dynamic stretching warm-up, 10-minute moderate-intensity cardiovascular training, 5-minute progressive resistance exercises, 5-minute proprioceptive neuromuscular facilitation, and 10-minute isometric stance maintenance. Certified exercise specialists will individualize each prescription by modifying intensity, duration, and modality based on comprehensive geriatric assessment, while maintaining core therapeutic components to ensure safety, efficacy, and sustainable adherence.

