		2.2.2 Sensations associated with cardiovascular and respiratory functions
Environmental factors	3.1 Support and relationships	3.1.1 Family life functions

Through a structured collaborative process involving physicians, participants, and caregivers, each individual will select three personalized goals. Under the research team’s guidance, participants will actively engage in both goal-setting and baseline evaluations, assessing each goal’s importance and anticipated difficulty on a 0–3 scale. These ratings will be multiplied to generate a weighted goal score. Outcome measurement will employ a 5-point scale (−2 to + 2) where − 2 indicates much worse than expected, −1 somewhat worse, 0 expected achievement, + 1 somewhat better, and + 2 much better than expected outcomes. This standardized approach ensures systematic evaluation while maintaining individualization of therapeutic objectives.

Goal Attainment Scaling (GAS) scores were calculated using a standardized formula and evaluated at baseline, 3-month, and 12-month follow-ups. An aggregated T score with a mean of 50 and an SD of 10 was obtained. T is the composite score, wi is the weight assigned to the ith goal, xi is the numerical value (− 2 to + 2) of the attainment level of the ith goal. The extent to which goals are achieved is standardised into a T score by the formula:$$\:GAS\:score=\:50\:+\:\:\:\:\frac{[10\sum\:\left(\text{w}\text{i}\times\:\text{x}\text{i}\right)]}{\surd\:[0.7\sum\:{wi}^{2}+{0.3\left(\sum\:wi\right)}^{2}]}$$

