### Outcomes

The primary outcome measure was Goal Attainment Scaling (GAS) score, which quantitatively assessed individualized goal achievement. The secondary outcome is the reversal rate of frailty, defined as a reversion from frailty to pre-frailty or non-frailty.

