### Organization of the trial

The trial is structured with two operational units: a working group overseeing study design and a data collection group managing participant interactions. To optimize protocol compliance, each participant will be assigned a dedicated study staff member who will coordinate data collection visits, address study-related inquiries, and provide ongoing support. Regular meetings will be implemented to monitor protocol adherence, identify potential implementation barriers, and resolve operational challenges in a timely manner. This dual-level organizational framework ensures both standardized data collection procedures and individualized participant engagement throughout the study duration.

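### As the protocol is ordered, GAS goals, levels and weights appear to be set after allocation, and nothing fixes them beforehand, so the primary outcome's yardstick could differ by arm

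*Protocol article*

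**What the plan says.** The Outcomes section names the primary endpoint: "The primary outcome measure was Goal Attainment Scaling (GAS) score". The abstract makes clear that both arms have goals: "All participants set personalized goals through GAS".

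The Randomization section gives the trigger for allocation: "Once a patient fulfills the criteria, after informed consent, participants will be randomly assigned to either the Usual care group or the Intervention group". It names no goal-setting step before allocation, and the eligibility criteria do not require a completed GAS form.

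The Intervention section starts with a comprehensive assessment to find the causes of frailty and continues: "Individualized treatment goals will be established using Goal Attainment Scaling (GAS), with subsequent implementation of personalized intervention plans".

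The section on formulating objectives and assessing efficacy says who sets the goals: "Through a structured collaborative process involving physicians, participants, and caregivers, each individual will select three personalized goals". It adds that, guided by the research team, "participants will actively engage in both goal-setting and baseline evaluations". Importance and difficulty are each rated 0 to 3: "These ratings will be multiplied to generate a weighted goal score". Level 0 on the five-point scale denotes the expected result.

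Two statements touch on masking, both under Randomization. One says the random numbers are generated blind. The other gives the envelope to a trial manager who takes no part in recruitment, assessment or intervention. Neither says that goal setters or scorers stay unaware of the arm.

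**The concern.** A conventional endpoint uses the same ruler for every patient. A GAS score does not, because the patient, caregiver and physician build the ruler by choosing three goals, describing five levels for each and rating two weight components. Randomisation protects the comparison only if that ruler is fixed without knowledge of the arm.

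If it is built afterwards, the expected level can come to mean expected under the allocated care. Bias could then run either way. Easier levels or favourable weights in the intervention arm would produce a difference that is not there. Expectations matched to each arm would draw both arms towards 50 and hide a real difference. No analysis could separate this from a treatment effect, because the two arms would have been measured on different rulers.

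Participants can hardly be masked to individualised intervention versus usual care, and they help set the goals and weights. Timing is therefore the main safeguard available for setting the ruler.

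**Working it through.** **Order of steps.** The sections set side by side:

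- Randomization: criteria met, then consent, then allocation.
- Intervention: assessment, then goals, then a plan built on the goals.
- Formulation of objectives: goal setting is paired with baseline evaluations, with no statement of before or after allocation.
- Abstract, Methods: all participants set goals; no timing is given.

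The first two put goal setting after allocation on their natural reading. The last two fit either order.

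**Inputs.** From the protocol: the GAS formula; three goals; a nominal T-score standard deviation (SD) of 10; 64 per group before attrition; alpha 0.05. Assumed: equal weights, a two-sided test, the share of patients affected and the direction.

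The plan's inflation for attrition reproduces: 64/(1 − 0.20) = 80 per group. The 64 was derived for frailty reversal, not for the GAS score, and serves here only as a group size.

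**Shift in one patient's score.** The formula is T = 50 + 10·Σ(w·x) / √[0.7·Σw² + 0.3·(Σw)²]. With three equal weights of 1, the denominator is √(0.7×3 + 0.3×9) = √4.8 = 2.191. For the same real outcome, unless the goal is already at the top level:

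- one goal set one level easier: 10/2.191 = 4.56 points;
- all three goals set one level easier: 30/2.191 = 13.69 points.

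**Effect of weights.** Weights run from 0 to 9. With weights 9, 1, 1 the denominator is √(0.7×83 + 0.3×121) = √94.4 = 9.716. One level on the heavy goal is then worth 90/9.716 = 9.26 points, and one level on a light goal 10/9.716 = 1.03. Identical attainment of +2, 0, −1 gives:

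- equal weights: 50 + 10/2.191 = 54.6;
- weights 9, 1, 1: 50 + 170/9.716 = 67.5;
- weights 1, 1, 9: 50 − 70/9.716 = 42.8.

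**From patient to arm.** If a share f of one arm has one goal set one level easier, the arm mean moves by f × 4.56. The standard error of the difference is 10·√(2/64) = 1.768. The difference detectable with 80% power is (1.960 + 0.842) × 1.768 = 4.95. With no true effect, the two-sided rejection rate is Φ(d/SE − 1.96) + Φ(−d/SE − 1.96):

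| Share f | Mean shift d | d/SE | Rejects, 64 per arm | Rejects, 80 per arm |
|---|---|---|---|---|
| 25% | 1.14 | 0.65 | 10% | 11% |
| 50% | 2.28 | 1.29 | 25% | 30% |
| 100% | 4.56 | 2.58 | 73% | 82% |

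**Hiding an effect.** Suppose the true difference is 5 points (an assumption) and the shift favours control. The chance of a significant result in the right direction with 64 per arm is Φ((5 − d)/SE − 1.96). It falls from 81% with no shift to 59%, 34% and 4% for the same three shares.

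The SD is held at 10 throughout. A partial shift would add at most 0.25 × 4.56² = 5.2 to a variance of 100 in one arm.

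**The case against.** The strongest reply is that section order in a journal article is not visit order. The abstract mentions goal setting before it describes what the intervention arm receives. Goal setting is paired with baseline evaluations, and the GAS score is also evaluated at baseline. The flow diagram, which may show the sequence, is not available here. Follow-up scoring is against levels defined in advance, and goals come from a finalised pool of 25. A condensed article may also leave masking to the full protocol.

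Much of this stands. A reader might infer that goals are definitely set after randomisation by a team that knows the arm. The article states neither: the timing is an inference from the order of the text, and silence on masking is not a statement that nobody is masked.

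A reader might also take the Organization of the trial section, where "each participant will be assigned a dedicated study staff member who will coordinate data collection visits, address study-related inquiries, and provide ongoing support", to mean that scoring is not separated from delivery. It does not say so. That person coordinates visits and gives support. The section does not say that this person scores GAS or delivers treatment, and the Intervention section gives delivery to specialists.

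Finally, 4.56 points is one patient's shift. It becomes an arm-level shift of that size only if every patient in one arm is affected and none in the other.

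Two things survive. Defining levels before scoring does not mean defining them before allocation. And the article does state a sequence: allocation on eligibility and consent, with goal setting as an opening step of the intervention. If goals are in fact set earlier, those two sections describe the order badly and still need correcting.

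**Conclusion.** The point holds as a defect in how the order is fixed, not as proof that goal setting is biased. Followed as written, the text lets the goals, expected levels and weights of the primary outcome be chosen with the arm known, and nothing in it prevents that.

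The possible damage ranges from modest to decisive. The false-positive rate is about 10% if a quarter of one arm is affected by one level on one goal, and 73% if all of it is (64 per arm). A shift favouring control could cost a comparable amount of power. These figures rest on equal weights, the nominal SD of 10, and an assumed share and direction; the documents give no evidence on the last two. The sample size of 160 is not affected.

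**What to change.** In the Randomization and Intervention sections, state that the comprehensive assessment and the GAS form (three goals, five level descriptions each, importance and difficulty ratings) are completed and locked for every participant before the envelope is opened.

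State also that attainment at 3 and 12 months is scored against the locked descriptions, where existing staffing allows, by a current data-collection staff member who has not been told the allocation. The article gives no staffing figures, so the sponsor has to judge whether this is feasible.

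The cost is small. Goal setting is already planned for both arms, so the change mainly reorders existing steps and leaves the sample size alone. The downside is that goals will also be set for a few people who leave before randomisation. If goals are already set first, only the wording has to change.

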### Justification of sample size

The sample size was calculated using a two-proportion comparison formula for a 1:1 randomized controlled trial, with an α of 0.05, 80% power, and an expected 20% absolute difference in frailty reversal rates between groups, based on prior intervention effect sizes. Initial calculations indicated 64 participants per group. Accounting for a 20% attrition rate, the adjusted sample size was 80 per group, resulting in a total of 160 participants. (http://powerandsamplesize.com/Calculators/)

